## Abstract

**Background:**

Diabetic nephropathy is the leading cause of end-stage renal disease (ESRD). Cardiovascular (CV) complications are the most common cause of death among ESRD patients. Beraprost sodium (BPS) is a prostacyclin analog with vasodilatory and antiplatelet effects.

**Methods:**

This is a multicenter prospective, randomized, double-blind, placebo-controlled trial to determine whether treatment with BPS improves arterial stiffness in patients with type 2 diabetic nephropathy. A total of 102 participants with type 2 diabetic nephropathy will be screened, enrolled, and randomly assigned to receive either 80 μg BPS or placebo daily for 12 weeks. The primary outcome is the change in brachial-ankle pulse wave velocity between baseline and after 12 weeks of medication use. The secondary outcomes will include changes in the ankle-brachial index, the urine albumin to creatinine ratio, the estimated glomerular filtration rate, lipid profiles, and blood pressure from baseline to after treatment.

**Discussion:**

This clinical trial is the first to investigate the effects of BPS on changes in CV biomarkers, albuminuria, renal function, and lipid profiles in patients with diabetic nephropathy.

**Trial registration:**

ClinicalTrials.gov number NCT01796418

## Background

The impact of diabetic nephropathy on the increasing population with chronic kidney disease (CKD) and end-stage renal disease (ESRD) is enormous. Diabetic nephropathy has become the leading cause of ESRD and is responsible for more than 40% of all cases in the USA and South Korea [1,2]. Although randomized studies have demonstrated that intensified multifactorial intervention in patients with type 2 diabetes reduces the risk of microangiopathy, cardiovascular (CV) events, and mortality [3-5], the incidence of ESRD due to diabetes is relentlessly increasing worldwide. CV complications are the number one cause of death among patients with ESRD [1,2]. Moreover, CV risk is not limited to ESRD, and the risk of CV mortality begins to increase with even a mild impairment of kidney function [6]. Therefore, early detection and intervention for CV complications are important to reduce mortality among patients with CKD or ESRD due to diabetes. In this regard, surrogate markers precisely estimating CV risk are essential. Pulse wave velocity (PWV) and the ankle-brachial index (ABI) are useful noninvasive biomarkers for predicting CV risk [7]. PWV provides a measure of large artery stiffness and has been reported as a risk factor for nonfatal CV disease and CV mortality independent of systolic blood pressure in dialysis patients [8,9]. The ABI is a clinical tool for the detection of peripheral arterial disease and the prediction of CV mortality and morbidity [10].

Beraprost sodium (BPS) is a stable orally active prostacyclin (PGI_2_) analog. BPS acts by binding to PGI_2_ membrane receptors and inhibiting the release of Ca^2+^ from intracellular storage sites. These effects lead to the relaxation of the smooth muscle cells and vasodilation. BPS has also been suggested to improve microvascular circulation through the reduction of red blood cell deformability. Moreover, BPS alleviates vascular thrombosis by inhibiting platelet aggregation. Through these vasodilatory and antiplatelet effects, BPS appears to be an effective agent in the treatment of patients with pulmonary arterial hypertension, Buerger’s disease, and arteriosclerosis obliterans [11].

An *in vitro* experiment showed that BPS improved endothelial function through the induction of nitric oxide (NO) production and endothelial NO synthase activation in endothelial cells [12]. In addition, BPS lowered serum vascular cell adhesion molecule-1 levels and prevented the increase of carotid intima-media thickness in patients with type 2 diabetes, which suggested a beneficial effect of BPS on the progression of atherosclerosis in diabetic patients [13]. The development of arterial stiffness, as assessed by PWV, has been prevented by BPS treatment in elderly patients with cerebral infarction [14,15]. BPS has also been shown to improve dyslipidemia and metabolic syndrome in diabetic animal models [16,17]. A recent study has reported that 8 weeks BPS treatment improves pain in diabetic patients with painful peripheral neuropathy [18]. However, no studies have observed the effects of BPS on CV biomarkers in diabetic nephropathy patients with a high risk of CKD or ESRD.

Based on reports of the beneficial effects of BPS, we hypothesize that BPS treatment will improve arterial stiffness in diabetic nephropathy patients. To evaluate this hypothesis, we will conduct this clinical trial in patients with type 2 diabetic nephropathy.

## Methods

### Hypothesis

Treatment with BPS will improve arterial stiffness in patients with type 2 diabetic nephropathy. Compared with placebo-treated patients, arterial PWV will decrease in BPS-treated patients.

### Study design

This is a multicenter prospective, randomized, double-blind, placebo-controlled trial. This study is an investigator-initiated clinical trial. The study algorithm is shown in Figure 1. After enrollment and treatment, clinical follow-up will be conducted after 4 and 12 weeks of treatment.

**Figure 1 F1:**
[figure not shown]
**Study algorithm.** BPS, beraprost sodium.

### Study participants

All patients aged 20 to 75 years with type 2 diabetes mellitus will be screened. The following will be performed at the initial visit: 1) questionnaire regarding past medical history and drug history; 2) physical examination of all systems; 3) measurement of height and weight; 4) blood pressure and pulse rate measurement; and 5) collection of blood and urine. Patients who meet all of the inclusion and exclusion criteria and provide written informed consent are eligible for this study (Table 1).

**Table 1 T1:** Inclusion and exclusion criteria

**Inclusion criteria**	**Exclusion criteria**
Age between 20 and 75 years	History of kidney transplantation
Type 2 diabetes using a glucose-lowering agent or insulin	Advanced congestive heart failure (≥ NYHA class III)
Estimated GFR by the IDMS MDRD equation ≥30 ml/min/1.73 m^2^	Uncontrolled arrhythmia
More than two UACR ≥30 mg/g or UPCR ≥ 300 mg/g in the most recent 6 months	Advanced liver cirrhosis (Child-Pugh class C)
Blood pressure ≤140/90 mmHg without any additional antihypertensive medications in the most recent 3 months	History of bleeding diathesis
	Active infection or uncontrolled inflammatory disorders
	History of cerebrovascular accident or myocardial infarction
	Current use of an anticoagulant
	Current use of more than two antiplatelet agents
	Advanced malignancy (life expectancy ≤6 months)
	Uncontrolled diabetes (HbA1C >10%)
	Severe anemia (hemoglobin <8.0 g/dL)
	Pregnancy or lactation
	Genetic disease including galactose intolerance, lactose deficiency, and glucose-galactose malabsorption

GFR, glomerular filtration rate; HbA1C, hemoglobin A1C; IDMS, isotope dilution mass spectrometry; MDRD, Modification of Diet in Renal Disease; NYHA, New York Heart Association; UACR, urine albumin to creatinine ratio; UPCR, urine protein to creatinine ratio.

Serum and urine creatinine (Cr) will be measured using the isotope dilution mass spectrometry-traceable method on a Toshiba TBA 200FR Analyzer (Toshiba, Tokyo, Japan). Urinary albumin will be measured using an immunoturbidimetric assay on a Toshiba TBA 120FR Analyzer. The estimated glomerular filtration rate (eGFR) is calculated using the Modification of Diet in Renal Disease formula. The formula was defined as follows, where the serum Cr concentration is in mg/dL: eGFR = 175 × Cr^−1.154^ × Age^−0.203^ × (0.742 if female) [19].

### Randomization

A research coordinator will perform the randomization and deliver the study drugs. The participants and investigators will be blinded to the treatment assignment. A list of random numbers will be generated by an independent statistician and then used to randomly allocate the treatments to equally sized treatment and control groups. The randomization will be stratified on the basis of sex and age, which will utilize a randomized block design in blocks of four patients in the order of enrollment in each arm. A randomization code list will be generated by a third party - the medical statistics support team in the Seoul National University Boramae Medical Center. The treatments will be allocated to the participants in accordance with the predefined randomization list (1:1 ratio for the treatment and control groups).

### Treatments

After randomization, the participants will take either a BPS (treatment group) or placebo (control group) pill during the study. The tablet shapes and packaging of the placebo pills are indistinguishable from those of the original BPS pills. The BPS and placebo tablets are provided by Astellas Pharma Korea, Inc. (Seoul, Korea). The prescription and administration of the study drugs will be performed in a double-blind manner. Based on the report showing the prevention of arterial stiffness with BPS [14], 80 μg/day BPS in two divided doses will be administered to the participants for 12 weeks. The administration of other prostacyclin agents, such as limaprost alfadex, or fluorinated pyrimidine antifungal agents, such as flucytosine, will be prohibited during the study. Participants with any changes in antihypertensive, antiplatelet, or anticoagulant medications during the study will be dropped. Investigators or research coordinators will evaluate drug compliance in the study participants, and participants with less than 80% compliance will be dropped from the study.

### Outcome measures

The primary outcome to be measured is the change in the brachial-ankle PWV (ba-PWV) between baseline and after 12 weeks of treatment. The secondary outcomes will include changes in the ABI, urine albumin to creatinine ratio, eGFR, lipid profiles, and blood pressure from baseline to after treatment.

### Clinical and laboratory evaluations

The physical examination and medication reviews will be performed before treatment and after 4 and 12 weeks of treatment. The laboratory evaluations, including a complete blood count, Cr, total cholesterol, triglyceride, low-density lipoprotein cholesterol, random urine albumin, and urine Cr, will be performed at baseline and after 12 weeks of treatment. ba-PWV and ABI will be measured using a Colin pulse waveform analyzer (Colin CO, Ltd, Komaki, Japan) at baseline and after 12 weeks of treatment. The study schedule is shown in Figure 2.

**Figure 2 F2:**
[figure not shown]
**Study schedule.** ABI, ankle-brachial index; ba-PWV, brachial-ankle pulse wave velocity; BP, blood pressure; BPS, beraprost sodium; Cr, creatinine; d, days; LDL, low-density lipoprotein; PR, pulse rate; R, randomization; T-chol, total cholesterol; TG, triglycerides; UACR, urine albumin to creatinine ratio; w, weeks.

### Monitoring and safety assessments

Before the start of this trial, a central monitor will review the study protocol and clinical research form (CRF) with the investigators and research coordinators. During the study period, a monitor will regularly visit each institute and evaluate the records of the participants, the CRF, compliance with the study protocol and Good Clinical Practice guidelines, and enrollment status. The storage, delivery, and accountability of the study drug will also be monitored during this period.

Any presence of bleeding, headache, hot flushes, shock, interstitial pneumonia, abnormal liver function, hypersensitivity reaction, angina, or gastrointestinal discomfort will be recorded during treatment with BPS/placebo. All adverse events, including serious adverse events (SAEs), will be recorded and followed-up for the duration of the study or until resolution. The assessment of adverse events will be performed by investigators and research coordinators. All SAEs will be graded and reported to the principal investigator and the ethics committee.

### Sample size calculations

No previous report has evaluated the effect of BPS on arterial stiffness in diabetic patients. We therefore referred to a study showing that the mean and standard deviation of the PWV change due to BPS treatment in patients with a history of cerebrovascular accidents were 260 cm/s and 345 cm/s, respectively [14]. We adjusted the sample size for an estimated drop-out rate of 25% due to poor compliance, a two-sided level of significance of α = 5%, and a power of 1-β = 90%, which indicated that 51 participants will be required in each group to detect a significant difference with a two-sided Student’s *t* test [20]. A total of 102 participants will be randomized and included in the analysis.

### Statistical analyses

The statistical analyses will be performed both on per protocol (PP) and intention-to-treat (ITT) bases. For the PP analysis, all participants who completed the study and were evaluated for the primary outcome will be included. For the ITT analysis, all participants who signed the written informed consent and were randomized into the study will be included, regardless of whether the correct treatment was administered. To evaluate the primary outcome, a PP analysis will be performed for those participants who showed a primary outcome variable among the targets for the PP analysis. The secondary outcomes will be evaluated in the participants who completed the study. For the safety evaluation, all participants who signed the written informed consent and were randomized to receive at least one of the active treatments (BPS/placebo medication) will be included in the analysis. The safety analysis will include the calculation of the frequencies and rates of complications and SAEs reported in the two groups.

The baseline clinical characteristics and laboratory data of the study participants will be summarized in terms of frequencies and percentages for categorical variables and means with standard deviations for continuous variables. Continuous variables will be analyzed using Student’s *t* test or the Mann–Whitney U test. Chi-squared test or Fisher’s exact test will be used for categorical variables. Differences in the changes in the outcome measurement variables between the treatment and control groups will be tested with one-way analysis of variance. Differences in the temporal changes in the outcome measurement variables in each group will be analyzed with the paired *t* test or Wilcoxon signed rank test. A value of *P* < 0.05 will be considered to be statistically significant. All analyses will be performed using SPSS (version 16.0. for Windows; SPSS Inc., Chicago, IL, USA).

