## Discussion

Diabetic nephropathy is the number one cause of ESRD. CV complications are the most common cause of death in ESRD. Therefore, the early detection of CV risk using biomarkers and the prevention of CV risk with an effective drug are the only ways to improve the clinical outcomes and mortality in patients with diabetic nephropathy. BPS, a PGI_2_ analog, has shown many beneficial effects in both preclinical and clinical studies. In this trial, we will test whether BPS improves CV risk. This trial is the first to investigate the effects of BPS on changes in CV biomarkers, albuminuria, renal function, and lipid profiles in patients with diabetic nephropathy.

Because BPS has the potential to increase bleeding risk by inhibiting platelet aggregation, even patients on a single antiplatelet agent appear to be in danger of bleeding after their enrollment in this study. However, higher doses of BPS administered for a longer duration compared with this study were previously reported to not increase bleeding risk. According to the study performed by Mohler and colleagues [21], daily intake of 120 μg BPS with other antiplatelet agents (aspirin, clopidogrel, or ticlopidine) for 1 year was not associated with any bleeding event. Furthermore, we will monitor and follow-up all adverse events, including bleeding, for the duration of the study or until resolution.

A 12-week study may be too short to demonstrate a beneficial effect of BPS. To assess the sustained effects of BPS on vascular benefits, long-term studies may be needed. However, in New York Heart Association functional class II and III patients with pulmonary arterial hypertension, a 12-week treatment with BPS improved exercise capacity and symptoms [22]. Moreover, the main mechanism of BPS in the improvement of arterial stiffness is through NO production, and BPS has a short half-life [12]. We therefore hypothesize that short-term treatment with BPS will improve arterial stiffness in this study. If the beneficial effects of BPS are proven, BPS could be used in clinical practice to improve CV and renal outcomes in this high-risk population. Future clinical trials with an extended administration of BPS over 52 weeks in a larger population will be required to determine whether BPS improves the actual CV morbidity and mortality.

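### The only analysis set assigned to the primary outcome is a per-protocol set shaped after randomisation, so the superiority comparison is open to bias in either direction

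*Protocol article*

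**What the plan says.** The Hypothesis section of the protocol article expects pulse wave velocity to fall on BPS relative to placebo, which is a superiority question.

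The Statistical analyses section opens with two bases: "The statistical analyses will be performed both on per protocol (PP) and intention-to-treat (ITT) bases". It defines ITT as everyone who consented and was randomised, whatever treatment they actually received, and defines PP as follows: "For the PP analysis, all participants who completed the study and were evaluated for the primary outcome will be included". It then allocates sets to outcomes. For the primary outcome: "To evaluate the primary outcome, a PP analysis will be performed for those participants who showed a primary outcome variable". For the rest: "The secondary outcomes will be evaluated in the participants who completed the study". No sentence gives ITT to a named efficacy outcome, and none says which result decides if the two differ.

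The Treatments section contains two removal rules that operate after randomisation: "Participants with any changes in antihypertensive, antiplatelet, or anticoagulant medications during the study will be dropped", and "participants with less than 80% compliance will be dropped from the study".

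The Sample size calculations section allows for 25% drop-out, yet counts all 102 randomised participants in the analysis. The Clinical and laboratory evaluations section schedules ba-PWV at baseline and week 12 only.

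**The concern.** Randomisation makes the arms comparable as randomised. A set reached by removing people for what happened to them on treatment loses that protection if the reasons for removal depend on treatment and relate to the outcome.

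The article supplies plausible routes. Of the drug's cellular actions, the Background says: "These effects lead to the relaxation of the smooth muscle cells and vasodilation". A vasodilator can prompt a change in antihypertensive treatment, and that change removes the participant. Blood pressure is also a secondary outcome, so removal is tied to a variable the trial itself thinks treatment may move. The Monitoring section lists headache, hot flushes and gastrointestinal discomfort among the events to record, and these can lower compliance. The Discussion adds that "BPS has the potential to increase bleeding risk by inhibiting platelet aggregation", which could lead to antiplatelet changes.

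At stake is the single primary comparison. An ITT result would normally reveal such a problem, but ba-PWV has one post-baseline measurement and the article describes none after a participant is dropped. A week-12 value that was never taken cannot be recovered later.

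**Working it through.** **1. The plan's own figure.** Inputs from Sample size calculations: difference 260 cm/s, SD 345 cm/s, two-sided α = 0.05, power 90%, drop-out 25%.

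- n per arm = 2 × (1.960 + 1.282)² × (345/260)² = 37.0, rounded up to 38. The noncentral t gives 37.99, also 38.
- 38 / (1 − 0.25) = 50.7, rounded up to 51 per arm, 102 in total. This matches.
- Power at 38 per arm is 90.0%.

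The arithmetic is right, and the stated power is that of the roughly 38 per arm left after losses. This fits a PP primary analysis. It does not fit the statement that all 102 enter the analysis.

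**2. How large the bias could be (illustration).** The article gives neither exclusion rates by arm nor any link between exclusion and PWV change. Assumptions: no true effect; SD 345; 25% lost in each arm; exclusion correlates r = 0.3 to 0.5 with PWV change on BPS and is uninformative on placebo.

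- Shift in the mean of the retained BPS participants = r × 345 × φ(z)/(1 − p). With p = 0.25, z = −0.674 and φ(z) = 0.318, the last factor is 0.318/0.75 = 0.424.
- r = 0.3: 0.3 × 345 × 0.424 = 44 cm/s, or 17% of 260.
- r = 0.5: 0.5 × 345 × 0.424 = 73 cm/s, or 28% of 260.
- Standard error with 38 per arm = 345 × √(2/38) = 79.1 cm/s, so the noncentrality is 44/79.1 = 0.55 or 73/79.1 = 0.92. With 74 degrees of freedom the critical value is 1.993.
- Two-sided type I error from the noncentral t: 8.5% (r = 0.3) to 15% (r = 0.5).

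**3. Direction.** Splitting those figures by tail, the side towards which the bias points rejects 7.9% to 14.7% of the time, and the other side 0.6% to 0.2%, against 2.5% each without bias. If the bias favours BPS, false claims of benefit rise. If it runs against BPS, they fall below 2.5% and a real effect is harder to show.

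**4. Sensitivity to the assumptions.** Same model, with selection in both arms:

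| Exclusion, BPS v placebo | Bias (cm/s) | Two-sided type I error |
|---|---|---|
| 25% v 25%, identical selection | 0 | 5% |
| 30% v 20% | 15 to 25 | 5.4% to 6.2% |
| 35% v 15% | 31 to 51 | 6.7% to 9.7% |

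Equal exclusion rates alone do not guarantee freedom from bias: step 2 has 25% in both arms.

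**5. Power if all randomised are analysed.** Assume the 25% who would be dropped keep a fraction f of the effect, so the difference is 260 × (0.75 + 0.25f), with SD 345 and a two-sided t test.

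| f | Difference (cm/s) | Power, 51 per arm | n per arm for 90% |
|---|---|---|---|
| 0 | 195 | 81% | 67 |
| 0.5 | 227.5 | 91% | 50 |
| 1 | 260 | 96% | 38 |

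If only 45 per arm are measured (an assumption) and f = 0, power is about 76%.

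**The case against.** The article does name an ITT analysis and defines it properly, and the sample size text counts all 102 in the analysis. A reader might infer that ITT is abandoned, or that it necessarily shrinks to the completers and cannot check the PP result. The article does not support that. It never says the week-12 visit is withheld from dropped participants. The medication-change rule says only that they are dropped, without saying from what, and final compliance may be known only at week 12, when ba-PWV is due anyway. How ITT would handle missing values can properly sit in a full protocol or SAP that is not shown. What remains is that only PP is assigned to the primary outcome, and that no measurement after dropping is described.

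A reader might also infer that the plan favours BPS. That does not follow. If vasodilation prompts antihypertensive changes, those removed could be the better responders, which biases towards no effect. Loss through intolerance or poor compliance could act differently.

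The bleeding route is weakened by the Discussion, which cites a study with no bleeding event at a higher daily dose taken with antiplatelet agents for a year. The blood-pressure and tolerability routes are untouched. All the routes are inferences from the pharmacology and listed events; the article does not say that BPS causes any exclusion.

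Finally, the magnitudes depend on chosen scenarios, and milder ones give little inflation. That is correct: they show what is possible and do not estimate what will happen.

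**Conclusion.** The point stands as a defect in the choice of analysis set. In a superiority trial, the one set assigned to the primary outcome depends on post-randomisation events that treatment could plausibly influence, and the secondary outcomes are confined to completers. The article also leaves this in conflict with its statement that all 102 are analysed.

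The size is unknown. Under the stated illustration the bias is about 44 to 73 cm/s and the two-sided type I error about 8.5% to 15%. Under identical selection in both arms there is none. The direction is not determined, so the conclusion is that the primary comparison is unprotected. It is not that a false claim of benefit is likely. Whether the ITT analysis could expose the problem depends on whether week-12 values are collected from dropped participants, which the article does not say.

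**What to change.** - In Statistical analyses, make ITT (all randomised, as randomised) the primary analysis for ba-PWV and for the secondary outcomes, with PP as supportive.
- In Treatments, state that participants with low compliance or a medication change stay in follow-up, and that the scheduled week-12 ba-PWV and laboratory measurements are taken regardless. Whether study drug is stopped is a separate clinical decision and is not at issue here.
- Reconcile the sample size text, which counts all 102 in the analysis, with the analysis sets and the 25% drop-out allowance.
- The imputation method for values still missing can be left to the SAP.

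Cost: revised wording, plus keeping an already scheduled visit for participants who would otherwise be dropped. The estimate may be diluted. At 102 participants, all measured, power is about 81% if non-compliers keep none of the effect, and lower if week-12 values are missing. Holding 90% in that case would take 67 per arm (134 in total) before any allowance for missing values. If non-compliers keep half the effect or more, the planned 51 per arm still gives at least 91% when all are measured.

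### The between-group test is valid and adequately powered on the plan's inputs, but an unadjusted ANOVA of change gives up precision that baseline ba-PWV and the randomisation strata could supply

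*Protocol article*

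**What the plan says.** The Outcome measures section defines the endpoint: "The primary outcome to be measured is the change in the brachial-ankle PWV (ba-PWV) between baseline and after 12 weeks of treatment". Under Clinical and laboratory evaluations, ba-PWV is measured "at baseline and after 12 weeks of treatment", so each participant in the comparison of changes has a baseline value.

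The Randomization section sets the allocation as "1:1 ratio for the treatment and control groups" and adds: "The randomization will be stratified on the basis of sex and age". It uses blocks of four.

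The Statistical analyses section then names the between-group test: "Differences in the changes in the outcome measurement variables between the treatment and control groups will be tested with one-way analysis of variance". A one-way analysis of variance has a single factor, here the treatment group. The other tests named there (t, Mann–Whitney, chi-squared, Fisher's exact, paired t, Wilcoxon) carry no covariates either. No covariate or stratum term appears anywhere in the article.

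The Sample size calculations section uses a two-sided Student's t test, for which the mean and standard deviation of the PWV change "were 260 cm/s and 345 cm/s, respectively". It takes 5% significance, 90% power and 25% drop-out, and arrives at 51 per group.

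**The concern.** The trial collects a baseline value of its primary measure and restricts allocation on two factors, yet the planned test uses none of this beyond subtracting baseline. Subtraction fixes the coefficient of baseline at 1. When the correlation between visits is below 1, the best coefficient is smaller, so the change score over-corrects. The treatment estimate then carries noise from chance differences in baseline ba-PWV between the arms.

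Stratified randomisation also makes the arms more alike on sex and age. If those factors predict the change in ba-PWV, a test that ignores them uses a standard error that is somewhat too large.

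What is at stake is the width of the confidence interval, and power if the true effect is smaller than assumed. The effect and standard deviation come from patients with a history of cerebrovascular accident, whom Table 1 excludes, so a smaller effect is possible.

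**Working it through.** **Inputs from the Sample size calculations section.** Difference 260 cm/s; SD of change 345 cm/s; two-sided alpha 0.05; power 0.90; drop-out 25%. The figure of 260 is taken as the between-group difference and 345 as the common SD of change, as the plan's calculation requires.

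**Step 1: reproduce the plan's figure.**
- n per arm = 2 × [345 × (1.960 + 1.2816) / 260]² = 37.001, rounded up to 38.
- The exact noncentral-t calculation also gives 38, with power 0.9001.
- 38 / 0.75 = 50.7, rounded up to 51 per arm, or 102 in total.

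The stated size is reproduced. A two-arm one-way ANOVA is the same test as the t test, so design and analysis agree.

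**Step 2: variance with baseline adjustment.** Let s be the SD at each visit (assumed equal) and ρ the correlation between baseline and week 12.
- Change score: variance 2s²(1 − ρ).
- ANCOVA: variance s²(1 − ρ²).
- Ratio, ANCOVA to change score: (1 + ρ)/2.

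The article does not give ρ, so a range is shown. The SD of change is held at 345 and one degree of freedom is charged for the covariate. The standard error (SE) of the planned test with 38 per arm is 345 × √(2/38) = 79.1 cm/s.

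| Assumed ρ | Variance ratio | SE, cm/s | Power, 38 per arm | Evaluable (randomised) per arm for 90% |
|---|---|---|---|---|
| planned test | 1 | 79.1 | 90.0% | 38 (51) |
| 0.5 | 0.75 | 68.5 | 96.3% | 29 (39) |
| 0.7 | 0.85 | 73.0 | 94.0% | 33 (44) |
| 0.8 | 0.90 | 75.1 | 92.7% | 35 (47) |
| 0.9 | 0.95 | 77.1 | 91.4% | 37 (50) |

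These figures are slightly favourable to ANCOVA. Estimating the slope from 76 participants costs on average a factor of 1 + 1/(76 − 4) = 1.014 in variance. The ratios at the two ends become about 0.76 and 0.96, which does not change the picture.

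**Step 3: a smaller true effect.** At 130 cm/s, half the assumed effect, power is 36.8% as planned. With baseline adjustment it is 46.5% at ρ = 0.5 and 38.3% at ρ = 0.9.

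**Step 4: chance baseline imbalance.** An imbalance of d in baseline ba-PWV shifts the change-score estimate by (1 − ρ)d. With s = 345/√[2(1 − ρ)], one standard error of d is s√(2/38). The shift is then:
- ρ = 0.5: 0.5 × 79.1 ≈ 40 cm/s
- ρ = 0.7: 0.3 × 102 ≈ 31 cm/s
- ρ = 0.8: 0.2 × 125 ≈ 25 cm/s
- ρ = 0.9: 0.1 × 177 ≈ 18 cm/s

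This is about 7% to 15% of 260 cm/s. The planned standard error already allows for this variation; ANCOVA removes it.

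**Step 5: sex and age.** This was simulated with four equal strata, blocks of four, 25% drop-out and 4000 runs per cell. The share of the variance in change explained by the strata is an assumption.

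| Share explained | Power, unadjusted | Power, adjusted | Type I error, unadjusted |
|---|---|---|---|
| 0 | 89.6% | 89.2% | 4.8% |
| 5% | 90.4% | 91.3% | 3.9% |
| 10% | 91.1% | 92.7% | 4.6% |
| 20% | 91.0% | 94.6% | 3.8% |

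The simulation standard error of each power figure is about √(0.9 × 0.1/4000) = 0.5 points, so the loss in the first row is within noise.

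**The case against.** The strongest reply is that nothing here is wrong. Under randomisation the planned test is unbiased and holds its significance level, it is specified in advance, and it is the test for which the trial was sized. All of this stands, and it limits the point to one of efficiency.

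The size of the gain is also uncertain. The correlation is not in the article, and at 0.9 adjustment adds only 1.4 points of power (91.4% against 90.0%). The strata help only if sex and age predict the *change* in ba-PWV, since differencing already removes stable differences in level. The article offers no evidence on this. Both objections stand for the size of the gain, but neither is a reason to leave a measured baseline out.

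It cannot be said that the matter was merely left to the analysis plan. The article names the test, and an analysis plan using ANCOVA would depart from it.

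A reader might infer more than the document supports:
- *That 38 evaluable per arm is too few because the test is unadjusted.* The 38 was calculated for exactly this test.
- *That regression to the mean biases the result.* Table 1 does not select on ba-PWV, and any such effect falls equally on both randomised arms in expectation.
- *That ignoring the strata inflates false positives.* The simulated error rates were all below 5%; if anything the test is conservative.
- *That site belongs in the model.* Site is not named as a stratification factor.

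**Conclusion.** The point holds as a recommendation on efficiency. The planned comparison is valid and delivers 90.0% power on the plan's own inputs. Adjusting for baseline ba-PWV would reduce the variance of the treatment effect by 25% (ρ = 0.5) to 5% (ρ = 0.9), and would raise power with 38 evaluable per arm to between 96.3% and 91.4%. The direction is secure across that range; the size is not. It rests on an assumed correlation, equal variances at the two visits, and the plan's SD of 345 cm/s. The gain from sex and age is conditional and may be nil, at negligible cost.

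The document does not support the stronger conclusions that the test is invalid or that the trial is underpowered because of it. Nor would adjustment repair the selection that may follow from dropping participants after randomisation; that is a separate matter.

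**What to change.** In the Statistical analyses section, replace the one-way ANOVA sentence, for the primary outcome, with an ANCOVA of week-12 ba-PWV (or its change) on treatment, baseline ba-PWV, sex and age. Report the adjusted treatment difference with its 95% confidence interval, and fix the model before unblinding, including whether age enters in its stratification categories or as a continuous variable. Do not add site as part of this change.

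For each secondary outcome, adjust for that outcome's own baseline. Use a suitable transformation, such as the logarithm, for skewed measures like the urine albumin to creatinine ratio, which has a lower entry limit but no upper one.

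The cost is a change of wording. All covariates are already collected, the model runs in the named software, and the sample size can stay as it is. With sex and age as single terms, the model uses three degrees of freedom, leaving 76 − 2 − 3 = 71 for error.
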